### Population and enrollment

Three hundred patients with ST elevation AMI (STEMI) submitted to successful mechanical (TIMI flow grade 3) or chemical recanalization of the culprit coronary artery up to 24 hours after symptoms onset, and presenting EF ≤ 50% will be selected for inclusion.

Patients will be eligible if presenting all the following characteristics: [1] STEMI; [2] age between 30 and 80 years; [3] EF ≤ 50% (Simpson) and [4] regional dysfunction in the infarct-related area, measured before cells injection. Among patients submitted to fibrinolytic therapy, the angioplasty of the related artery should be done up to 72 hours after fibrinolysis. All patients will be treated with Liberte™ stents, generously donated by Boston Scientific Corp., Natick, Massachusetts.

Patients will be excluded if presenting any of the following: obstruction >50% on Left Main Coronary Artery or multivessel coronary disease, indicating the need for CABG (Coronary Arterial Bypass Grafting); coronary anatomy presenting no need for angioplasty with stent implant; final diastolic pressure of left ventricle (LV) higher than 30 mm Hg during initial ventriculography; cardiac arrest or Killip IV at admission with the need of ventilatory support; cardiogenic shock persisting up to the third day after symptoms onset; mechanical complications of AMI; significant valve disease; chronic use of immunosuppressant agents; >2,0 mg/dl creatinine or previous dialysis treatment; sepsis; sustained ventricular tachycardia after 48 hours post-AMI; illicit drugs abuse or alcohol abuse (based on DSM IV); myocarditis; active liver disease; severe COPD (Chronic Obstrutive Pulmonary Disease); hematological disease, neoplasm, bone disease or haemostatic disturbances; inflammatory disease or chronicle infectious disease; presence of definitive implantation of a cardiac pacemaker or cardiac defibrillator or any co-morbidity, with survival impact in 2 years.

Patients will be included only after signing Informed Consent form, written in accessible language and with information about all relevant aspects regarding the research protocol.

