### Sample size

Sample size calculation was performed according to the following assumptions:

▪ Based on Pró-Cardíaco Hospital and InCor's coronary care databank, after selecting AMI patients Killip I; II or III, we have concluded that the left ventricle EF presented a Gaussian distribution with an average of 37.35% and standard deviation of 7.9%).

▪ An expert panel has evaluated that an improvement of +5% (relative gain of +15.9%) on the EF would represent a significant clinical improvement for the patient.

Considering as clinically beneficial a 5% increase in EF% with a standard deviation of 5%, 143 patients per arm are needed to detect a significant difference between groups with 95% confidence and 80% power. Considering a 5% loss during follow up, we estimated 150 patients per arm.

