### End points and statiscal analysis

The primary endpoint of this trial is the global left ventricular EF change from baseline to 6 month follow-up.

The following secondary endpoints will be evaluated for up to 1 year of follow up: major cardiovascular events (all-cause mortality, acute myocardial infarction, stroke and hospital admission due to cardiovascular cause); reintervention of the AMI-related artery and of non-related arteries; by MRI regional wall motion, wall thickening, and volume of late contrast enhancement; quality of life assessment using the Short-Form 36, Minnesota Living with Heart Failure and Seattle Angina questionnaires; cost-effectiveness and cost-utility evaluation of ABMMC implant versus conventional treatment.

All outcomes will be analyzed by intention to treat.

Primary outcome will be analyzed by comparing EF, measured by MRI, between groups, using student t test or Mann-Whitney according to the sample distribution. Two evaluations are programmed:

1. Interim analysis, which will use data related to patients 1 to 150;

2. Final analysis, which will use data related to all 300 patients.

Secondary outcomes will only be evaluated after the main final analyses. Mortality and functional class improvement will be analyzed by non-corrected chi-square test. Continuous variables with normal distribution will be analyzed by t student test and ANOVA for repeated measures. Continuous variables with asymmetric distribution and quality of life scores will be analyzed by Mann-Whitney test and ANOVA for repeated measures.

The frequency of serious adverse events (which brings eminent risk of death or permanent disability) will be analyzed by chi-square or Fisher's test.

The trial can be interrupted after interim analysis; using the O'Brien and Fleming rule for two sequential tests and the 5%, in which the null hypothesis is rejected if:

• p ≤ 0,0050 in the first analysis;

• p ≤ 0.04806 in the final analysis.

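### The primary EF test, as written, includes only patients with the needed MRI scans, although the plan describes it as intention to treat on all 300 patients

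*Protocol article*

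**What the plan says.** Four statements in the protocol article bear on this.

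- **Endpoint** (End points and statistical analysis): "The primary endpoint of this trial is the global left ventricular EF change from baseline to 6 month follow-up".
- **Test** (same section): "Primary outcome will be analyzed by comparing EF, measured by MRI, between groups, using student t test or Mann-Whitney according to the sample distribution". No other primary method is given.
- **Principle and analysis set** (same section): "All outcomes will be analyzed by intention to treat". Two looks follow: "Interim analysis, which will use data related to patients 1 to 150" and "Final analysis, which will use data related to all 300 patients".
- **Expected loss** (Sample size): "Considering a 5% loss during follow up, we estimated 150 patients per arm". The number needed before that allowance is 143 per arm.

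All-cause mortality is part of a secondary endpoint, so deaths are foreseen. The article does not link them to the EF comparison.

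On timing, patients are randomized on the day of injection, after marrow aspiration planned for days 5 to 7. The baseline MRI is set for days 6 to 9 after recanalization, and Table 2 lists it under the post-injection visits. Table 2 also schedules echocardiograms at days 3 to 5 and at 1, 3, 6 and 12 months.

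**The concern.** The stated principle, patient set and test do not fit together. A t test or Mann-Whitney test needs a value from each patient it includes. A patient with no 6-month MRI has none, and if change is analysed, neither has a patient with no baseline MRI. The default is therefore to drop these patients.

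Dropping them matters when the reason for a missing scan is related to outcome. The trial enrols patients with EF of 50% or below after infarction, and those who die or become too ill to return may well have had the lower EFs. A comparison restricted to survivors with scans depends on events that treatment may itself affect. A report calling it intention to treat would claim more protection from randomization than the analysis has.

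**Working it through.** **1. Patients with data under the plan's own loss rate.**

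- The plan's inflation step: 143 / 0.95 = 150.5, which rounds up to 151. The article states 150, which is close enough.
- Read the other way: 150 × 0.95 = 142.5 per arm, or 300 × 0.95 = 285 in total.

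The sizing thus treats lost patients as contributing no value, whereas the analysis section speaks of all 300.

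**2. Which scans can be lost after randomization.**

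- Randomization: day of injection, after an aspiration on days 5 to 7.
- Baseline MRI: days 6 to 9, possibly at a reference hospital. Discharge is predicted 24 hours after the cell procedure.
- Second MRI: 6 months.

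The change endpoint therefore needs two scans, and either can be missed after allocation.

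**3. Bias of the complete-case difference.** Let *m* be the share of an arm without a value, and *D* the gap between the mean EF of scanned patients and the mean that unscanned patients would have had.

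- Full-arm mean = scanned mean − *m* × *D*.
- Error in the difference (cells minus control) = *m*(cells) × *D*(cells) − *m*(control) × *D*(control).

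With a common gap this is *D* × [*m*(cells) − *m*(control)]. The inputs below are assumptions; none is in the documents.

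| Lost, control | Lost, cells | Gap *D* | Error (EF points) |
|---|---|---|---|
| 5% | 5% | any | 0 |
| 7% | 3% | 10 | −0.4 |
| 8% | 2% | 10 | −0.6 |
| 10% | 5% | 5 to 15 | −0.25 to −0.75 |
| 15% | 5% | 5 to 15 | −0.5 to −1.5 |

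The negative sign means that the cells look worse than they are. If the cell arm lost more, the sign would reverse. For patients who die there is no EF to recover, so the formula covers missed scans better than deaths.

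**4. Scale.** SE = SD × √(2/142).

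- SD 7.9 (the article's databank figure): 0.94, so 0.4 to 0.6 point is 0.43 to 0.64 SE.
- SD 5 (the article's design figure): 0.59, so 0.4 to 0.6 point is 0.67 to 1.01 SE.

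**5. Power.** The design inputs are "Considering as clinically beneficial a 5% increase in EF% with a standard deviation of 5" percent. At two-sided 5% and 80% power, a 5-point difference needs 16 per arm at SD 5 and 40 per arm at SD 7.9. With 20% loss (120 per arm) and the final threshold of 0.04806, power is still at least 99.8% at either SD. (That 143 does not follow from 5 points and SD 5 is a separate matter.)

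**The case against.** The strongest reply is that this is mostly an omission. Rules for missing scans and deaths are commonly left to a full protocol or analysis plan, and neither is shown. A t test can follow imputation, and a Mann-Whitney test can give deaths the worst rank. The phrase about all 300 sits in a list opposite the interim look at patients 1 to 150, so it may only describe enrolment at each look. The 5% loss is stated openly, and mortality has its own analysis.

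Much of this stands. The absence of a missing-data rule is not in itself the point, and nothing is concealed. What remains is that the article does name a principle, a set and a test, and they do not agree with each other or with the loss allowance.

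Three stronger readings are tempting, but the documents do not support them.

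- **Inflated false claims of benefit.** Under the assumed shifts, with no treatment effect and a 1.96 cut-off, total rejection would be 7.1% to 9.8% at SD 7.9 and 10.3% to 17.3% at SD 5. Almost all of it is in the tail against the cells. The tail in their favour falls from 2.5% to between 0.1% and 0.9%. Moreover, excess control loss because the cells work cannot be the mechanism when they do not work.
- **Devices implanted during follow-up prevent the MRI.** The article mentions devices only as an entry exclusion ("presence of definitive implantation of a cardiac pacemaker or cardiac defibrillator"). The rest is inference.
- **Too few patients.** If each scan were missed independently by 5%, 150 × 0.95 × 0.95 = 135 per arm would remain, fewer than 143. The second 5% is not in the documents, and step 5 shows no real shortfall at either stated SD.

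**Conclusion.** The point holds as an inconsistency that is cheap to repair, not as a demonstrated bias. By the plan's own loss rate about 285 of 300 patients would supply the primary outcome. The test as written compares survivors with the needed scans, under an intention-to-treat label.

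The size of any bias cannot be derived from the documents. It is zero with equal loss and an equal gap in both arms, and 0.4 to 0.6 EF point under the assumed 10-point gap with splits of 7%/3% or 8%/2%. Against a target difference of 5 points that is modest. If controls lose more low-EF patients, it would understate the effect of the cells. The conclusion assumes that no unseen document adds a rule for deaths and missing scans; if one does, only the article's wording needs aligning.

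**What to change.** - **Analysis set.** Restate it as all randomized patients, and reconcile the reference to all 300 with the 5% loss allowance.
- **Primary analysis.** Analyse 6-month MRI EF by arm, with baseline EF in the model, using multiple imputation or a linear mixed model. Use the scheduled echo EF (days 3 to 5 and 1, 3 and 6 months) as auxiliary data. Baseline EF keeps the analysis aligned with the change endpoint.
- **Deaths.** Prespecify one analysis that ranks deaths before 6 months below every observed value.
- **Sensitivity.** Prespecify one tipping-point analysis showing how much lower the unscanned patients' EF would have to be, by arm, to change the conclusion.
- **Reporting.** Give the number scanned at each time point by arm, with the reason for each missing scan.

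The cost is wording and some programming, with no new visits, scans or patients. The primary result would rest on a stated missing-at-random assumption. That assumption does not resolve truncation by death, since the model would in effect assign an EF to patients who died, which is why the worst-rank analysis is needed beside it.

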#### ✓ Baseline exams (before bone marrow aspiration) and follow up

The chronogram of the study is shown in table 2. Briefly, patients will be submitted to a clinical evaluation at hospital admission and clinical data regarding blood pressure, heart rate and Killip and Kimball classification will be stored. Patients will be standardly treated with chemical or mechanical reperfusion according to the local center availability. A coronary angiography and an invasive ventriculography will be performed in all patients before angioplasty in order to evaluate inclusion/exclusion criteria. Patients submitted to fibrinolysis must have the angioplasty of the infarct-related coronary artery performed up to 48 hours after reperfusion. Laboratorial dosage will be also performed as shown in table 2.

**Table 2 T2:** Chronogram of the study

Informed Consent	□											
Randomization				□								

**Exams/Visits**					**After Injection**							
										
	Baseline	pos-reperfusion	3^rd^–5^th ^day of reperfusion	5^th ^to 7^th ^day	Up to 1 h	12 h	24 h	6^th ^to 9^th ^day	1 month	3 months	6 months	1 year

Medical visit	□		□						□	□	□	□
ALT, AST, AP, PT, aPTT and INR			□									
Total Cholesterol, LDL-cholesterol, HDL-cholesterol and Triglycerides	□											
Full blood panel, Glucose, Urea, Creatinine, Na+, K+, CRP			□				□		□		□	
CK-MB mass, Troponin I	□		□	□		□	□					
Electrocardiogram	□	□	□		□	□	□		□	□	□	□
Echocardiogram			□						□	□	□	□
Cardiac MRI								□			□	
Coronary angiography	□										□	
Cells transplant				□								
Cells sample storage				□								
SF-36, Minnesota and Seattle QOL			□						□		□	□
QALY Evaluation									□		□	□

ALT and AST: alanine and aspartate aminotransferases, respectively; AP: alkaline phosphatase; INR: international normatized ratio; PT: prothrombin time; aPTT: activated partial thromboplastin time; CRP: C-reactive protein; MRI: magnetic resonance image; QOL: quality of life questionnaires; QALY: quality adjusted life year.

Three to five days after reperfusion therapy (mechanical or chemical), patients will be submitted to another clinical evaluation, including an EKG, an echocardiogram and laboratory tests, from which results will be used as baseline data for the research protocol, before injection procedure. A new CK-MB mass and troponin dosage will be performed in the morning preceding the injection procedure and timely in the 24 hours following the injection.

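### Quality-of-life scores are assigned both a rank test and a normal-theory repeated-measures ANOVA, with no governing result and a method that in its classical form needs every visit

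*Protocol article*

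**What the plan says.** The Protocol article, section *End points and statiscal analysis*, sorts the continuous secondary variables by distribution. For the normal ones: "Continuous variables with normal distribution will be analyzed by t student test and ANOVA for repeated measures". For the others: "Continuous variables with asymmetric distribution and quality of life scores will be analyzed by Mann-Whitney test and ANOVA for repeated measures". The same ANOVA therefore appears in both classes. No transformation, rank-based ANOVA or mixed model is named, and no order is set between the two methods.

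The same section states: "All outcomes will be analyzed by intention to treat". It lists among the secondary endpoints "quality of life assessment using the Short-Form 36, Minnesota Living with Heart Failure and Seattle Angina questionnaires", and it defers all secondary outcomes until after the main final analysis.

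In Table 2 (section on baseline exams and follow up) the row "SF-36, Minnesota and Seattle QOL" carries four marks, which I read as days 3 to 5 after reperfusion, 1 month, 6 months and 1 year. The cardiac MRI row carries two: days 6 to 9, and 6 months.

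On losses, the *Sample size* section says: "Considering a 5% loss during follow up, we estimated 150 patients per arm".

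**The concern.** The only reason to leave the t test for these variables is that a normal-theory method is thought unsuitable. Applying another normal-theory method to the same variables undoes that decision.

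Three things are at stake for the quality-of-life scores.

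- **Choice of result.** Each score yields a Mann-Whitney result and one or more ANOVA results. Without a rule, whichever is favourable can be reported as the finding.
- **Patients used.** Classical repeated-measures ANOVA needs a complete set of visits from each patient. A patient with one missed questionnaire contributes nothing, although the plan promises intention to treat for every outcome.
- **Quantity estimated.** With four time points, the group or group-by-time F test does not by itself give the treatment difference at 6 or 12 months, which is what a reader of these secondary results will want.

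**Working it through.** **1. The plan's own loss figure.** Inputs from *Sample size*: 143 per arm, 5% loss, 150 per arm. 143 / 0.95 = 150.5, so the stated 150 is reproduced to rounding. Total loss: 0.05 × 300 = 15 patients. The 143 itself is not reproduced: a difference of 5 with SD 5 gives 2 × (1.96 + 0.84)² × 5² / 5² = 15.7, or 16 per arm. That is a separate matter. Here 143 serves only as the size used in the simulation below.

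**2. Patients with complete quality-of-life data.** The plan gives no missed-visit rate. Assume a rate m at each of the three follow-up visits, independent across visits. The complete share is (1 − m)³.

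| m (assumed) | (1 − m)³ | complete of 300 | dropped by a complete-case ANOVA |
|---|---|---|---|
| 2% | 0.941 | 282 | 18 |
| 5% | 0.857 | 257 | 43 |
| 10% | 0.729 | 219 | 81 |

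If the baseline questionnaire can also be missed, the exponent is 4 and the complete counts are 277, 244 and 197.

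At m = 5%, a single-visit test at 6 or 12 months would use 0.95 × 300 = 285 patients, while the ANOVA would use 257. The two prescribed methods would then rest on patient sets that differ by 28. The share with no follow-up score at all is 0.05³ = 0.000125, or 0.04 of 300, so a method using all observed visits keeps nearly everyone.

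**3. What skew does to the ANOVA.** A simulation used 143 per arm, four visits and a correlation of 0.7 between adjacent visits that decays with lag. The skewed data were lognormal with log-scale SD 1. Correlation and distribution are assumptions. There were 4,000 null runs, so the Monte Carlo standard error near 5% is √(0.05 × 0.95 / 4000) = 0.0034.

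| false-positive rate at nominal 5% | lognormal | normal |
|---|---|---|
| ANOVA group effect | 0.044 | 0.052 |
| ANOVA group-by-time, uncorrected | 0.058 | 0.065 |
| ANOVA group-by-time, Greenhouse-Geisser | 0.043 | 0.048 |
| Mann-Whitney, last visit | 0.047 | 0.050 |
| Mann-Whitney or corrected group-by-time | 0.084 | 0.088 |
| either of these or the group effect | 0.116 | 0.121 |

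Skew does not inflate any single test. The small uncorrected excess also appears with normal data, so it comes from the correlation pattern. The rise to 8.4% and 11.6% comes from having two or three tests with no rule between them, and it too is present without skew.

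With a shift of 0.3 log units at all follow-up visits (2,000 runs), power was 43% for group-by-time ANOVA on the raw skewed scale, 73% for the same ANOVA on the log scale, and 71% for Mann-Whitney at the last visit. The first two figures are the like-for-like comparison. The third uses one visit and no baseline.

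**4. MRI outcomes.** With two time points sphericity holds trivially, and the group-by-time F test is the square of the t test on change. It therefore does give the 6-month comparison, and it needs no more data than any change-score test. For a skewed MRI measure, only the pairing of a rank test with a normal-theory test remains.

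**The case against.** The strongest reply is that the two methods answer two questions: Mann-Whitney compares the groups at a visit, and the ANOVA describes the course over time. The same pairing is used for normal variables, which supports that reading, and Mann-Whitney would then supply the 6- and 12-month comparisons. Ranking secondary tests and handling missed visits are also commonly left to an analysis plan, which is not shown here and might use a mixed model.

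Part of this stands. Silence on missing data is not a fault in this article. A reader might infer that the protocol says patients with a missed visit will be dropped. It does not: that is a property of the classical form of the method it names. A reader might also take 43 of 300 as the plan's expected loss, but the plan's 5% is a total, which gives about 15. Nor do the documents support a claim that the complete-case results are biased, since no pattern of missingness is given. Echocardiography has more visits in Table 2 but is not a listed endpoint, so it adds nothing.

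The reply does not remove the stated choice itself. A normal-theory method is prescribed for variables set apart as unsuitable for normal theory, and the two-question reading is not written down. A mixed model in the analysis plan would be a change from the method named here, so the sentence would still need correcting.

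**Conclusion.** The point holds in a limited form, and it is minor. The plan is inconsistent with itself on asymmetric variables and quality-of-life scores, and it leaves open which of two methods governs. The practical effect falls on the three quality-of-life instruments. The primary endpoint, the sample size and the stopping rule are untouched.

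On size: about 15 of 300 patients are lost to a complete-case ANOVA if 5% is total loss. Intermittent misses would raise that to 18, 43 or 81 at assumed independent rates of 2%, 5% or 10% per follow-up visit. Calling a score positive on either of two methods gave about 8% false positives in the simulation.

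A reader might infer that skew makes the ANOVA invalid. At about 143 per arm the simulation does not support that. The cost is power, and its size (43% against 73%) depends on the assumed lognormal shape and shift, neither of which comes from the protocol.

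**What to change.** For the quality-of-life scores, replace the repeated-measures ANOVA with one mixed model for repeated measures: treatment, visit, treatment-by-visit and the baseline score, fitted to all observed follow-up visits. Name the 6-month and 12-month treatment contrasts as the governing results. Because this model also assumes normal errors, state that a transformation or bootstrap will be used where skew is marked. Keep Mann-Whitney as a sensitivity check. MRI outcomes need only a statement of which test governs.

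The cost is a change of wording and slightly more programming, with no new data. The downside is that the model relies on data being missing at random given the observed scores. It also recovers nothing for a patient who has no follow-up questionnaire at all.

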### Randomization

A computer-random number generator will perform randomization procedure in the day of injection as previously published in Trials.[11] Briefly, software was created in R version 1.9.0 to specifically generate the randomization sequence for the study. It is known that a simple randomization is sufficient and efficient to render the study groups homogeneous for known and unknown factors in large scale clinical trials. To insure homogeneity in the two arms of the study we adopted block randomization. We will use randomization by variable size block (blocks of 2, 4 or 6 patients). Patients will be randomized after bone marrow aspiration and only the hematologist responsible for cell separation will have the login and password to randomize the patient online. According to the assigned group, darkened syringes containing the mononuclear cell fraction or saline with 5% autologous serum will be then prepared and sent for injection.

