### Cell transplantation Phase

#### ✓ Bone marrow aspiration procedure

About 100 ml of bone marrow aspirate will be harvested from iliac crest between the 5^th ^and 7^th ^day after myocardial reperfusion therapy under local anesthesia and sedation at an intensive care unit or surgical center. The aspiration procedure will be done by using a 1.8 mm Jamshidi needle.

ABMMC will be isolated by density gradient centrifugation on Ficoll- Paque™ plus^® ^(Amersham Biosciences) and manipulated under aseptic conditions. 100 × 10^6 ^cells will be resuspended in 10 ml saline solution with 5% autologous serum and filtered through 100 μm nylon mesh to remove cell aggregates for injection. A fraction of the cell suspension will be used for cell counting and viability testing with trypan blue exclusion. Cell viability must be above 90% to be injected. Post-hoc characterization of leukocyte differentiation markers by flow cytometry (table 1) and functional assays will be done on another fraction of cells. This last evaluation concerns clonogenic capacity of marrow progenitors by colony-forming assays (granulocyte-macrophage colony-forming units – CFU-GM, vascular-endothelial cell colony-forming unit – CFU-VE, and fibroblast colony-forming assay – CFU-F), as previously described.[12,13]

**Table 1 T1:** Post-hoc characterization of leukocyte differentiation markers

**Phenotype**	**Intended designation**
**1**. CD45^lo^CD34^+^	ISHAGE protocol
**2**. Lin^-^CD45^lo^CD34^+^	Hematopoietic progenitors
**3**. Lin^-^CD45^lo^CD34^+^CD133^+^CD117^+^	Hematopoietic stem cells*
**4**. Lin^-^CD45^-^CD133^+^CD31^+^CD144^+^KDR^+^	Endothelial precursor*
**5**. Lin^-^CD45^-^CD133^-^CD31^+^CD144^+^KDR^+^	Endothelial cell*
**6**. CD45^+^CD10^+^CD33^+^HLA-DR^-^CD45RA^-^	Myeloid precursor*
**7**. CD45^+^CD10^+^CD33^-^HLA-DR^+^CD45RA^+^	Lymphoid precursor*
**8**. CD45^-^CD133^+^CD146^+^CD144^+^CD166^+^	Mesenchymal progenitor*
**9**. CD45^-^CD133^-^CD146^+^CD73^+^CD166^+^	Mesenchymal cell*
**10**. CD45^+^CD10^+^CD34^+^CD19^-^CD38^-^TdT^+^IgM^-^	pre-pro-B intermediary
10.1. CD45^+^CD10^+^CD34^+^CD19^+^CD38^-^TdT^+^IgM^-^	pro-B/pre-B I intermediary
10.2. CD45^+^CD10^+^CD34^-^CD19^+^CD38^-^TdT^-^IgM^-^	Pre-B II intermediary
10.3. CD45^+^CD10^-^CD34^-^CD19^+^CD38^+^TdT^-^IgM^+^CD24^hi^	Immature B LΦ
10.4. CD45^+^CD10^-^CD34^-^CD19^+^CD38^+^TdT^-^IgM^+^	Naïve B LΦ
10.5. CD45^+^CD10^-^CD34^-^CD19^+^CD38^+^TdT^-^IgM^+^CD24^lo^CD69^+^	Mature B LΦ

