The baseline cardiac magnetic resonance imaging (MRI) will be performed between day 6 and 9 after the AMI-related coronary artery recanalization. This exam may be performed either in the hospital or at a reference hospital. All imaging exams will be evaluated off line by the core lab specified in the appendix [see Addition file 1].

Hospital discharge is predicted 24 hours after cell transplantation unless otherwise indicated, making a total length of stay of approximately 7 days. Patients will be provided with clopidogrel, aspirin and pravastatin during the entire study and treated at the discretion of the attending physician.

Patients will be followed for 1 year after the procedure according to the chronogram of the study shown in table 2. All imaging exams will be stored and sent to the core lab for independent analysis as specified in the appendix [see Addition file 1].

Cardiac MRI will be done by the local centers with commercially available software, electrocardiographic triggering, and cardiac-phased array coil. LV function will be assessed by the use of steady-state free-precession gradient-echo sequence (SSFP). Eight to twelve short axis slices will be acquired during a 10–15 seconds breath-holding allowing for coverage of the entire LV. Additionally, 3 long-axis views will also be acquired: 2-chamber and 4-chamber views and left ventricle out flow tract. Regional LV function will be assessed by measuring systolic wall thickening in the infarct region, the adjacent border zone and remote myocardium and semi-quantitatively assessed, using a 17-segment model[14].

Transmural extent of late hyper-enhancement within each segment will be graded according to the following classification: 0–25%, 26–50%, 51–75%, and more than 75% hyper-enhancement. Segmental functional recovery is defined as an increase from hypokinetic to normokinetic, from akinetic to hypokinetic or normokinetic, or from dyskinetic to akinetic, hypokinetic, or normokinetic. Infarct size will be measured by planimetry.

Microvascular obstruction will be defined on late enhanced images taken early (within 2–5 min) after injection of 0.20 mmol/kg of gadopentetate dimeglumine (Gd-DTPA), in the LV short and long axis at the same locations used for cine-MRI–as a dark, subendocardial zone within the infarct area.

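### The printed definition of a serious adverse event omits events that require or prolong hospitalization, so some product-related harms fall outside every listed event endpoint

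*Protocol article*

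**What the plan says.** The protocol article, under End points and statistical analysis, gives one criterion and one test for serious adverse events: "The frequency of serious adverse events (which brings eminent risk of death or permanent disability) will be analyzed", the test being chi-square or Fisher's. The word printed as eminent is read here as imminent.

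The same section lists the other event endpoints, introduced by "The following secondary endpoints will be evaluated for up to 1 year of follow up". They include "major cardiovascular events (all-cause mortality, acute myocardial infarction, stroke and hospital admission due to cardiovascular cause" and, as a separate item, "reintervention of the AMI-related artery and of non-related arteries". Mortality also has its own planned chi-square test.

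Three design facts bear on the point:
- Harvest is invasive: "About 100 ml of bone marrow aspirate will be harvested from iliac crest" (Bone marrow aspiration procedure).
- The order is fixed: "Patients will be randomized after bone marrow aspiration" (Randomization).
- The index stay ends soon after infusion: "Hospital discharge is predicted 24 hours after cell transplantation unless otherwise indicated" (Baseline exams and follow up).

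**The concern.** The printed criterion has two limbs, risk of death and permanent disability. It has none for an event that puts a patient in hospital or keeps one there. The trial adds an invasive harvest, a manipulated cell product and an intracoronary infusion to an index stay that is expected to end a day later. Many non-fatal complications of such a sequence would show up as a delayed discharge or a later admission for a non-cardiac reason.

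If those events are not serious by definition and not cardiovascular by composite, they enter no listed event comparison. The trial could then follow its definition exactly, report no excess of serious events, and still have had more product-related hospital days or non-cardiovascular admissions in the cell arm. The primary ejection-fraction result is not affected. What is at stake is how complete the safety statement is.

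**Working it through.** The article gives no event rates and no figure to reproduce. The check is one of classification: take each kind of harm and see which listed endpoint would count it. In every row, assume that the event poses no imminent risk of death and causes no permanent disability, unless the row says otherwise.

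| Harm | SAE test | Cardiovascular composite | Reintervention | Counted? |
|---|---|---|---|---|
| Death | yes | yes | – | yes |
| Infarction or stroke, including in the index stay | if severe enough | yes | – | yes |
| New admission for a cardiovascular cause | no | yes | – | yes |
| Repeat intervention on any coronary artery | no | – | yes | yes |
| Infusion harm that only prolongs the index stay | no | no (not a new admission) | no | **no** |
| Non-cardiovascular harm that prolongs the index stay | no | no | no | **no** |
| Non-cardiovascular harm that causes a later admission | no | no | no | **no** |

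The last three rows are the gap. The parenthesis can also be read as risk of death, or permanent disability that has actually occurred. That reading changes nothing, because hospitalization is absent either way.

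**Which uncounted harms can differ between arms?**
1. Aspiration comes before randomization, so every randomized patient in either arm has been harvested. Iliac-crest bleeding or infection should be equally frequent in both arms.
2. Controls receive saline with autologous serum through the same blinded intracoronary procedure. Access-site and catheter harms should also balance.
3. The arms differ in the cells: marrow separated by density gradient, handled, resuspended and infused about 6 hours after harvest, against a solution without cells. Infection, fever or other non-cardiovascular illness due to the product can therefore differ.

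The gap that matters for a comparison is thus the product-related part of the three uncounted rows.

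**Scale.** With 150 patients per arm, one uncounted patient is 1/150 = 0.67 percentage points. If the uncounted class has an excess of *d* percentage points in the cell arm, and does not overlap with the counted class, the printed criterion understates the excess by exactly *d*. The value of *d* is unknown. Two assumed cases show the range:
- *d* = 0: the comparison is not distorted, and only the description of harms is incomplete.
- *d* = 5 points, taken as 8% against 3%: 150 × 0.08 = 12 patients against 150 × 0.03 = 4.5. With narrowly defined events at 2% in each arm (150 × 0.02 = 3), the printed criterion shows 2% against 2%, while the full count is 2 + 8 = 10% against 2 + 3 = 5%.

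These rates are assumptions. They show how an excess could go unseen and are not evidence that there is one.

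**The case against.** The strongest reply is that the article condenses a larger programme. It refers to an already published parent protocol, to paper and electronic case report forms, and to an independent data and safety monitoring committee. Rules for collecting and reporting adverse events commonly sit in such documents. Table 2 also schedules cardiac markers and electrocardiograms at 12 and 24 hours, and a blood panel with C-reactive protein at 24 hours, so early harm would be looked for. This stands as far as it goes: the article does not say that other adverse events go unrecorded. It does not remove the point, because the seriousness criterion is printed and attached to a named test, and as written that test counts only events that meet it.

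A reader might also infer four stronger things that the article does not support.
- *That all harvest and infusion harms leading to a hospital stay are missed.* Procedural death, infarction and stroke, cardiovascular admission and reintervention are all listed endpoints.
- *That harvest or access-site harms could hide an excess in the cell arm.* Both arms are aspirated and infused, so these should balance; counting them mainly improves description.
- *That this is the only between-arm safety test.* Mortality has its own chi-square test, and cardiovascular events and reintervention are listed outcomes.
- *That imminent risk is an unusually subjective standard.* Deciding what is life-threatening also takes judgement. The most that can be said is that a hospitalization limb is easier to verify.

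Finally, widening the definition adds events that are common to both arms, and these add noise to the pooled comparison. That is true and is a cost of the change.

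**Conclusion.** The point holds in a limited form. The stated definition omits events that require or prolong hospitalization. As a result, non-cardiovascular harms that cause or prolong a stay, and harms that only prolong the index stay, fall outside the SAE test, the cardiovascular composite and the reintervention endpoint, unless they threaten life or cause permanent disability. For the between-arm comparison the loss is mainly product-related harm; for harvest harm it is mainly a loss of description.

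The size cannot be fixed from the article. It runs from no distortion, if the uncounted class is balanced, to the whole of whatever excess lies in that class. The conclusion assumes that the test is run on the criterion as printed and that the index stay is not itself classed as a cardiovascular admission. The matter is worth correcting because the safety statement depends on it and the change is cheap. It has no bearing on the primary endpoint.

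**What to change.** In End points and statistical analysis, replace the parenthesis after serious adverse events with: *any adverse event that results in death, is life-threatening, requires or prolongs hospitalization, or causes persistent or significant disability*.

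Then state two things:
- The arms are compared on events from randomization to 1 year, using the planned chi-square or Fisher's test. The count should not start at aspiration, because patients have no arm until they are randomized.
- Events between aspiration and randomization are described separately, without a between-arm test.

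The cost is one definition, the matching case report form field, and more events to record and classify. Events already recorded may need reclassifying, and this should be finished before any unblinded analysis. Reporting the events that meet the present criterion as a subset would keep the narrower count visible and offset the added noise.
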